### Intervention and control condition

Participants randomised to the intervention arm will get access to an mHealth app aimed at lifestyle behavioural change, supported by a coach. This interactive app facilitates self-management of dementia risk factors (hypertension, dyslipidaemia, active smoking, overweight, lack of physical exercise and unhealthy diet). The participants will be supported by an experienced lifestyle coach trained in motivational interviewing, who will be matched to the ethnicity of the participants with one of the coaches able to speak Turkish for Turkish participants. The coaches will assist participants in formulating simple, measurable, achievable, realistic and time-bound (SMART) goals and support them in achieving these goals. Their role is to guide them in their lifestyle change. They are instructed to recommend participants with medical questions to seek help from their doctor. Also, mental health-related questions are beyond the scope of our intervention, and will result in a recommendation to visit their doctor. Participants can contact the coach via the app through chat, and coaches will be motivated to stay in contact with the participants at least once a month. After secure login, the app shows the participants’ dementia risk profile, based on baseline assessment. Participants can set goals for lifestyle change, monitor these goals and enter self-measurements, for example, weight, blood pressure and physical exercise. Progress over time is visually presented whenever feasible. Additionally, the app contains evidence-based education modules, including educational videos specifically designed for this study population, featuring the health coaches. The intervention app will be available in three versions for each ethnicity, with culturally acceptable content. The two versions for the Dutch and South-Asian Surinamese population will be available in Dutch; the version for the Turkish population will be available in both Dutch and Turkish. Those randomised to the control condition will have access to an app which is similar in appearance, but lacks the interactive features of coach-support and monitoring risk factors. Participants are informed that there are two versions of the app and that they will be randomly assigned to one. They are not made aware that one app serves as the active intervention while the other represents the control condition. The control app provides only static information about healthy lifestyles, without incorporating culturally specific content, and is available in both Dutch and Turkish.

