(6) Intervention costs	Costs of coaches and app intervention development
(7) Cost-effectiveness	Cost-effectiveness analyses are clarified in online supplemental appendix 1
(8) Cognitive functioning	The Rowland Universal Dementia Assessment Scale^26^ and the Box Task^27^
(9) Daily distance moved	Behapp, a remote behavioural monitoring app^28^

The implementation of the intervention will be measured using implementation outcomes reflecting coverage, acceptability, adoption, appropriateness, feasibility, fidelity, costs and sustainability.^29^ All implementation outcomes and evaluation methods are shown in table 2.

**Table 2 T2:** Summary of implementation research methods and outcomes

Method	Implementation outcome^7^	Measurements	Population	When measured
Quantitative	Coverage	(Non)response rates, comparison characteristics participants with eligible/source population	Potential target population	At baseline
	Adoption	Quantitative analysis of the utilisation, usage and uptake—for example, logins, goals setting, sending messages	All intervention participants	After 1 month (data features)
	Appropriateness	Short questionnaire of perceived fit or relevance*	All intervention participants	After 6 months and at study end
	Acceptability	Short questionnaire of agreeability, user-friendliness, credibility, complexity, content*	All Intervention participants	After 6 months and at study end
	Feasibility	The extent to which the mHealth intervention can be carried out	All intervention participants	After 6 months and at study end
	Sustainability	Adherence, dropout, data features (time spent in the app)	All intervention participants, dropouts	Data features throughout the study
	Implementation cost	Implementation costs (see cost-effectiveness analysis plan in online supplemental appendix 1)	n.a.	After 6 months and at end of study
Qualitative	Appropriateness	Perceived fit or relevance of the intervention	Intervention participants†; coaches	After 6 months
	Adoption	Initial utilisation, usage and uptake	Intervention participants†	After 6 months
	Acceptability	Agreeability, user-friendliness, credibility, complexity, content	Intervention participants†; coaches	After 6 months
	Feasibility	Practical and social barriers/facilitators related to the feasibility of the intervention	Intervention participants†; coaches	After 6 months
	Fidelity	Degree to which the mHealth application is implemented compared with the original protocol	Coaches	After 6 months

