## Statistical analysis and quality assurance

### Sample size

The sample size was calculated based on the expected effect of the intervention on our primary effectiveness outcome in individuals with low education, used as a proxy for low SES, from our previous prevention trials. In participants with a low educational level in the HATICE trial,^16^ the mean difference between intervention and control participants in change from baseline was 0.107 (pooled SD 0.454) for the composite z-score after 1.5 years. In the preDIVA trial,^30^ the difference in composite z-score between individuals with a low educational level who developed dementia and those who did not during 6–8 years of intervention was 0.096 after 24 months. Therefore, a mean difference in change of 0.107 was considered as potentially clinically relevant with respect to the risk of dementia. For the effect of the intervention within specific migrant groups, no data are available. With 277 participants per treatment arm, we will have 80% power (with alpha set at 0.05) to detect a 0.107 (pooled SD 0.454) difference on our primary effectiveness outcome. To adjust for an anticipated drop-out of 20% in this specific target population, 692 participants will be recruited.

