### Data analysis

The primary effectiveness outcome is the difference between the composite z-score after 12 months and the baseline composite z-score ((z_SBP_+z_non-HDL cholesterol_+z_BMI_)/3). The baseline mean and SD will be used to calculate composite z-scores at both time points to be able to detect a change. For the primary analyses, we will use a linear mixed effects model with individual observations nested within ethnic groups, operationalised by a random intercept and/or slope (depending on best model fit). If needed, we will explore the impact of any baseline imbalances by including imbalanced factors as a covariate in a sensitivity analysis. A per-protocol analysis will be done, based on uptake within the first month and continued use during the whole intervention period. Exploratory subgroup analyses on the primary outcome will be performed for ethnic group, sex, age group, history of CVD and diabetes.

We will conduct a sensitivity analysis using multiple imputation for the primary effectiveness outcome. Implementation of the intervention will be analysed with a series of implementation outcomes, as summarised in table 2. We will investigate frequency of app use and contact with the coach in relation to the effect on the primary outcome. We will graphically portray the Likert scales for the questionnaires and perform thematic analysis for the in-depth interviews. The interview guides can be found in the online supplemental appendix 3.

For the secondary outcomes, the effect on the CAIDE dementia risk score and its individual components (ie, blood pressure, BMI, total cholesterol, physical activity) will be analysed using the same model as for the primary analysis. In addition, as an exploratory analysis, the effect on daily changes in general movement will be assessed based on the data collected with the BeHapp application.^28 31 32^ For that purpose, time series analysis will be performed to detect trends in this longitudinal data as a function of intervention, accounting for clustering within ethnicities.

Scales for disability, depressive symptoms and cognitive functioning, mostly ordinal, will also be analysed as linear scales if the data characteristics allow. The same model as used for the primary analysis will be employed. Poisson regression or zero-inflated models may be applied to distributions resembling count or zero-inflated data. A description of the cost-effectiveness analysis can be found in online supplemental appendix 1.

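### The per-protocol analysis selects on app use after randomisation, and use means different things in the two arms, so the estimate is open to selection bias of unknown size

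*Protocol article*

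**What the plan says.** The Data analysis section commits to the analysis in one sentence: "A per-protocol analysis will be done, based on uptake within the first month and continued use during the whole intervention period". It does not say whether the rule applies to one arm or both, and it mentions no adjustment for selection. A later sentence in that section adds: "We will investigate frequency of app use and contact with the coach in relation to the effect on the primary outcome".

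The section on the intervention and control condition shows how the apps differ. The control app "lacks the interactive features of coach-support and monitoring risk factors". The same section adds: "The control app provides only static information about healthy lifestyles, without incorporating culturally specific content". Intervention participants also have a coach who is encouraged to be in touch at least monthly.

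Table 2 measures adoption at one month by items such as "logins, goals setting, sending messages", and sustainability by adherence and time spent in the app throughout the study. Both are listed for intervention participants (with dropouts added for sustainability). No usage measure is listed for controls.

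The primary analysis is separate: "For the primary analyses, we will use a linear mixed effects model with individual observations nested within ethnic groups".

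**The concern.** Taking up an app in the first month and still using it at one year reflects motivation, health and circumstances as well as the app itself. People who do so may have improved more anyway. Intervention users can also enter weight and blood pressure and see their progress, and these bear on two of the three components of the primary outcome. Those who improve may keep going and those who do not may stop, so selecting on year-long use could select partly on outcome, through feedback that the control app lacks.

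One usage rule would pick out different kinds of people in the two arms, and a rule applied to one arm would compare a selected group with an unselected one. Either way the contrast is no longer a randomised one. The analysis of app use and coach contact has the same weakness: coach contact exists in one arm only, so what it yields is an association, although the sentence speaks of an effect.

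At stake is how an estimate in sustained users is read. A reader could take it as the effect of the app in those who use it, when some or all of it may be selection.

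**Working it through.** **The plan's own figure.** The Sample size section gives: "With 277 participants per treatment arm, we will have 80% power (with alpha set at 0.05", and the target is "to detect a 0.107 (pooled SD 0.454) difference on our primary effectiveness outcome". The usual two-sided formula gives n = 2 × (1.96 + 0.84)² × 0.454² / 0.107² ≈ 283 per arm, against 277 stated. Power at 277 is 79.2%. Dropout: 554 / 0.8 = 692.5, against 692. The figures reproduce closely enough. They neither support nor weaken the present point, but they supply the SD and the yardstick.

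**Inputs.** From the Sample size section: SD 0.454, target 0.107, 277 per arm. Assumed, because the article gives neither: the share p retained as users, and the correlation ρ between propensity to use the app and the improvement that would occur without it. Improvement is counted as positive.

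**Filter on the intervention arm only, all controls kept.** With normal selection, bias = ρ × SD × φ(t) / p, where t is the normal cut-off that leaves a share p above it.

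- Low end, ρ = 0.1 and p = 80%: φ(t)/p = 0.280/0.8 = 0.350, so bias = 0.1 × 0.454 × 0.350 = 0.016, or 15% of 0.107.
- High end, ρ = 0.3 and p = 40%: φ(t)/p = 0.386/0.4 = 0.966, so bias = 0.3 × 0.454 × 0.966 = 0.132, or 123% of 0.107.

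The table gives the bias and, in brackets, how often a nominal 5% test rejects when there is no true effect. The standard error is 0.454 × √(1/(277p) + 1/277), with the SD taken as unchanged by selection.

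| ρ | 40% kept | 60% kept | 80% kept |
|---|---|---|---|
| 0.1 | 0.044 (13.8%) | 0.029 (10.1%) | 0.016 (6.7%) |
| 0.2 | 0.088 (40.5%) | 0.058 (25.9%) | 0.032 (12.1%) |
| 0.3 | 0.132 (73.2%) | 0.088 (50.4%) | 0.048 (21.4%) |

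**Filter on both arms.** The bias is the difference between the two selection shifts. At ρ = 0.2:

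| Kept, intervention | Kept, control | Bias |
|---|---|---|
| 60% | 80% | +0.027 |
| 60% | 60% | 0 |
| 60% | 40% | −0.029 |
| 80% | 20% | −0.095 |

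The zero in the second row also assumes that use has the same relation to outcome in both arms, which the difference between the apps makes doubtful.

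**Check on the remedy.** With one-sided non-compliance, the complier-average causal effect (CACE) is the intention-to-treat (ITT) effect divided by p. It is valid only if assignment does nothing for those classed as non-compliers. Suppose compliance means sustained use, p = 50%, and partial users get half the users' effect Δ (all assumed). Then ITT = 0.5Δ + 0.5 × 0.5Δ = 0.75Δ. With ITT = 0.107, Δ = 0.107/0.75 = 0.143, but CACE = 0.107/0.5 = 0.214, which is 0.071 too high. A sustained-use threshold is therefore a poor definition of compliance.

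**The case against.** The fair case against has several parts.

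- A reader might infer that the plan sets selected intervention users against all controls. The article does not say so. Table 2 points that way, but it defines implementation outcomes, not the per-protocol set. Controls have an app of similar look whose use could be counted, and the arm, threshold and any adjustment may be set out in a fuller document. That silence is not the finding; selection on use after randomisation is what the article itself fixes.
- A reader might infer that the analysis will overstate efficacy. That is too strong. Upward bias is the likely direction only if the intervention arm alone is filtered and use goes with improvement that would occur anyway. With both arms filtered the sign is open.
- A reader might take the Discussion's remark about healthier, more motivated participants as support. It concerns entry into the trial, affects both arms and is raised as a matter of generalisability. It says nothing about who keeps using the app.
- A reader might infer that the main result is compromised. It is not: the per-protocol analysis is separate from the primary model, and no decision is tied to it.
- An instrumental-variable estimate has its own upward bias when partial users benefit. This stands, and it determines how compliance should be defined.

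**Conclusion.** The point holds in a limited form. The planned per-protocol comparison conditions on use after randomisation, in a trial where use is not comparable between arms, so it is open to selection bias. With an intervention-only filter the bias is about 0.016 to 0.132 z-units, from a small fraction of the 0.107 target to more than all of it. That range rests on assumed correlations of 0.1 to 0.3, on 40% to 80% retained and on normal selection; none of these comes from the article. With a filter in both arms the sign is uncertain. The primary analysis is not affected, so this is a matter of improving and correctly labelling a secondary analysis.

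**What to change.** - Make the main adherence analysis a complier-average causal effect with randomised arm as the instrument (for example two-stage least squares), adjusted for baseline composite score and ethnicity.
- Define compliance minimally, as any uptake of the intervention app in the first month, so that no effect in non-compliers is plausible. The app is already downloaded before randomisation for the questionnaires, so uptake should mean use of the intervention app after allocation.
- Show stricter thresholds, including sustained use, as sensitivity analyses only, with a note that they tend to overstate the effect when partial users benefit.
- Keep the sustained-use per-protocol comparison as supportive, state which arms the rule applies to, and name its selection bias.
- Report the relations of app use and coach contact to outcome as associations within the intervention arm, not as effects.

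The cost is wording and one extra model, a wider interval than the intention-to-treat estimate, and an exclusion-restriction assumption that must be stated. Controls have no planned access to the coached app, so non-compliance is essentially one-sided, apart from the contamination that the Discussion acknowledges. Design, recruitment and data collection do not change.

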### Primary and secondary outcomes

Following a type 2 hybrid effectiveness-implementation design, equal weight will be placed on the effectiveness and implementation outcomes. The primary effectiveness outcome will be the difference between baseline and 12 months follow-up of a composite z-score of systolic blood pressure, non-high-density lipoprotein (HDL) cholesterol and body mass index (BMI). The secondary effectiveness outcomes include changes from baseline in CAIDE dementia risk score,^21^ individual modifiable components of the CAIDE risk score, questionnaires on physical activity,^22^ disability,^23^ depressive symptoms^24^ and cognitive functioning,^25 26^ cost-effectiveness analysis including intervention costs and daily distance moved measured by Behapp. Depressive symptoms are an outcome, because indirect effects may occur, for example, through increased physical activity. Cognitive functioning will be tested with The Rowland Universal Dementia Assessment Scale (RUDAS) and the Box Task for a computerised assessment of visuospatial working memory.^27^ Two parallel forms of the RUDAS were created for repeated administration at the beginning and end of the trial. Daily distance moved will be measured using a separate smartphone application (Behapp), which is optional and for which separate informed consent will be asked. Behapp has been developed and is operated by The University of Groningen to provide a remote, unobtrusive and objective measure of overall social mobility in a longitudinal daily-life manner. An in-depth explanation of Behapp, as well as the privacy and security measures, deployed by Behapp are described in detail previously.^28^ Effectiveness outcomes are summarised in table 1.

**Table 1 T1:** Effectiveness outcomes

Primary outcomes
Composite score of systolic blood pressure, non-HDL cholesterol and body mass index (BMI)

Secondary outcomes	Measurement tool
(1) Physical exercise	Self-administered short International Physical Activity Questionnaire-Short Form^22^
(2) Disability	WHO Disability Assessment Schedule 2.0 (12-item)^23^
(3) Depressive symptoms	Geriatric Depression Scale 15-item^24^
(4) CAIDE dementia risk score	Cardiovascular Risk Factors, Ageing and Dementia^21^
(5) Individual modifiable components of the CAIDE risk score	Age (≥47 years), education (<10 years), sex, systolic blood pressure, obesity (BMI ≥30), physical activity and total cholesterol

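### Physical activity is given the primary outcome's linear change model with no distribution condition; baseline adjustment on a stated scale would recover power at almost no cost

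*Protocol article*

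**What the plan says.** The primary model is described in the protocol article, Data analysis: "we will use a linear mixed effects model with individual observations nested within ethnic groups". The outcome it serves is a change: "The primary effectiveness outcome is the difference between the composite z-score after 12 months and the baseline composite z-score". The third paragraph of the same section lists the CAIDE components, ending with "physical activity) will be analysed using the same model as for the primary analysis". Nothing in that sentence makes the choice depend on how the activity data look.

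The next paragraph treats other scales more cautiously: "Scales for disability, depressive symptoms and cognitive functioning, mostly ordinal, will also be analysed as linear scales if the data characteristics allow". It then adds a general permission: "Poisson regression or zero-inflated models may be applied to distributions resembling count or zero-inflated data".

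Table 1 lists physical exercise as secondary outcome (1), measured with the "Self-administered short International Physical Activity Questionnaire-Short Form", and lists physical activity again under secondary outcome (5), the CAIDE components. The article does not say whether the CAIDE component is a continuous score, a category or a yes/no item. It gives no mean, SD, share of zeros or expected effect for activity.

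**The concern.** A total activity score cannot fall below zero and can run far above its typical value. If it is markedly right-skewed, a difference in mean raw change is driven by a few very high reporters and is an inefficient test of a shift in the whole group. Subtracting baseline rather than adjusting for it adds noise whenever the correlation between visits is moderate. That second loss applies whether activity is scored continuously or as yes/no.

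The section on the intervention and control condition counts activity among the app's six targets (the list ends "active smoking, overweight, lack of physical exercise and unhealthy diet"). A real behavioural effect could therefore be missed for reasons of analysis alone. What is at stake is efficiency on one secondary outcome, not the validity of its test.

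**Working it through.** **The plan's own figure.** The Sample size section gives 277 per arm for a difference of 0.107, SD 0.454, 80% power and alpha 0.05 (two-sided assumed):

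n = 2 × (1.960 + 0.842)² × 0.454² / 0.107² ≈ 283 per arm.

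Power at 277 is 79.2%, and 554 / 0.8 = 692.5 against the stated 692. The figure reproduces closely, but it concerns only the composite z-score ("a mean difference in change of 0.107 was considered as potentially clinically relevant"). Activity has no stated power to reproduce.

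**Assumptions for a continuous score (none is in the article).** Log-normal scores, log-scale SD σ from 0.3 to 1.2, log-scale correlation ρ = 0.5 between visits, 277 per arm. The effect is multiplicative and sized so that a baseline-adjusted log analysis has 80% power:

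log effect = 2.8016 × σ × √(1 − ρ²) × √(2/277).

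The mixed model is approximated by a two-group comparison without the ethnicity term.

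**Simulated power, 2,000 runs per row**

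| σ | Effect ratio | Raw change | Log change | Log, baseline-adjusted | Rank, baseline-adjusted |
|---|---|---|---|---|---|
| 0.3 | 1.064 | 65.2% | 66.7% | 79.2% | 76.6% |
| 0.5 | 1.109 | 62.7% | 69.0% | 79.8% | 78.2% |
| 0.8 | 1.179 | 51.5% | 67.8% | 79.4% | 77.5% |
| 1.0 | 1.229 | 41.4% | 69.0% | 79.7% | 76.8% |
| 1.2 | 1.281 | 36.4% | 68.5% | 80.2% | 77.8% |

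- Loss from skew alone (log change minus raw change): 1.5, 6.3, 16.3, 27.6 and 32.1 points.
- Loss from change rather than baseline adjustment (log adjusted minus log change): 12.5, 10.8, 11.6, 10.7 and 11.7 points.
- Type I error of the raw-change test: 4.3% to 5.6%.

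**Closed-form check.**

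- *Log change:* its variance is 2σ²(1 − ρ) = σ², against 0.75σ² after adjustment. Power is Φ(2.8016 × √0.75 − 1.96) = Φ(0.466) = 68%, as simulated.
- *Raw change at σ = 1.0:* the raw variance is (e − 1)e = 4.671 and the raw correlation is (e^0.5 − 1)/(e − 1) = 0.378. The mean difference is e^0.5 × 0.229 = 0.378. The change variances are 5.815 (control) and 7.391 (intervention). So z = 0.378 / √(13.206/277) = 1.73, and power is Φ(1.73 − 1.96) ≈ 41%, as simulated.

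**With zeros.** With 5% zeros, a true 25% increase and ρ = 0.5, power for raw change, linear baseline-adjusted and rank baseline-adjusted was:

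- σ = 0.8: 71%, 82%, 88%
- σ = 1.0: 44%, 57%, 72%
- σ = 1.2: 26%, 36%, 55%

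With 10% zeros placed at random in the first set-up, an adjusted analysis of log(x + 0.1) fell to 14–47%, while the rank analysis held 51–53%. A plain log transform is therefore not a safe repair.

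**If activity is a yes/no item.** Assume 40% active at baseline in both arms, 40% versus 50% at 12 months, and latent correlation 0.5. The baseline–follow-up covariances are then 0.0791 (control) and 0.0804 (intervention).

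- *Change:* variances 0.24 + 0.24 − 2 × 0.0791 = 0.322 and 0.24 + 0.25 − 2 × 0.0804 = 0.329. So z = 0.10 / √(0.651/277) = 2.06, power 54%.
- *Baseline-adjusted:* residual variances 0.24 − 0.0791²/0.24 = 0.214 and 0.25 − 0.0804²/0.24 = 0.223. So z = 0.10 / √(0.437/277) = 2.52, power 71%.

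The gap is 17 points. Simulation over latent correlations of 0.4 to 0.6 gave 52–58% against 72%. This loss comes from analysing change; a linear model of the 12-month item with baseline as covariate would not suffer it.

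**The case against.** The best case for the plan has four parts.

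- **Which outcome the sentence governs.** It concerns the CAIDE component, whereas Table 1 attaches the IPAQ to a separate outcome. This stands: the article does not fix how the component is scored, so both readings have to be worked. Under either one, analysing change is inefficient.
- **Flexibility.** The permission for Poisson or zero-inflated models names no outcome. It might reach activity, so a reader should not infer that the plan rules out every alternative. But it is optional, follows the sentence on the other scales, and addresses counts and excess zeros rather than a heavy-tailed continuous score. It does not clearly qualify the unconditional statement about activity.
- **Assumed skew.** A reader might infer that activity is known to be strongly skewed and that most of the power is thrown away. The article gives no distribution, and at σ of 0.3 to 0.5 skew costs only about 2 to 6 points. Nor may the whole gap between raw change and an adjusted rank analysis be blamed on skew, since 11 to 13 points of it come from baseline adjustment.
- **Form of effect and choice of tests.** A multiplicative effect favours log and rank methods. With an additive effect, however, raw change still reached only 67% (σ = 0.5) and 64% (σ = 1.0), against 80% and 81% for linear baseline adjustment. The adjusted rank analysis also beat raw change across σ of 0.3 to 1.2. The rank analysis stands in for the proportional-odds model, which was not itself simulated.

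It is also fair that scale and transformation are often left to an analysis plan. Here, though, the article has already named the model.

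**Conclusion.** The point holds as a conditional loss of efficiency. The article gives activity the primary linear change model and withholds the distribution condition granted to three other scales. For a continuous score, the cost of skew depends on an SD the article does not supply and becomes large only from a log-scale SD of about 0.8. The further cost of using change rests on a correlation near 0.5 and on reading the assigned model as one of raw change without baseline as covariate, which is how the primary outcome is defined. For a yes/no item the loss is about 15 to 20 points under the assumed 40% versus 50%.

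A reader might infer that a positive activity result would be untrustworthy. The calculations do not support that, since type I error stays near 5%. The primary outcome and its sample size are untouched.

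**What to change.** In Data analysis, remove physical activity from the outcomes that share the primary model, and state the scale on which it is analysed. Then specify, before unblinding:

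- **IPAQ total:** the 12-month value in a rank-based or proportional-odds model with baseline activity and ethnicity as covariates, and the baseline-adjusted mean difference as supportive.
- **CAIDE yes/no item, if used:** a binary model of the 12-month item with the same covariates.

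Say which of the two answers Table 1 outcome (1) and which answers outcome (5).

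This is a change of wording only. The questionnaires are already completed at baseline and repeated at study end, so no data or participants are added. The price is that the main effect measure for the IPAQ total is no longer in activity units, which is why the mean difference should be shown beside it.
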